# Design of a randomized controlled trial on the effect on return to work with coaching plus light therapy and pulsed electromagnetic field therapy for workers with work-related chronic stress

**DOI:** 10.1186/s12889-016-3276-6

**Published:** 2016-07-19

**Keywords:** Work-related chronic stress, Burnout, Light therapy, Pulsed electromagnetic field therapy (PEMF), Work participation, Stress, Fatigue, Quality of life

## Abstract

**Background:**

Work-related chronic stress is a common problem among workers. The core complaint is that the employee feels exhausted, which has an effect on the well-being and functioning of the employee, and an impact on the employer and society. The employee’s absence is costly due to lost productivity and medical expenses. The usual form of care for work-related chronic stress is coaching, using a cognitive-behavioural approach whose primary aim is to reduce symptoms and improve functioning. Light therapy and pulsed electromagnetic field therapy are used for the treatment of several mental and physical disorders. The objective of this study is to determine whether coaching combined with light therapy plus pulsed electromagnetic field therapy is an effective treatment for reducing absenteeism, fatigue and stress, and improving quality of life compared to coaching alone.

**Methods/design:**

The randomized placebo-controlled trial consists of three arms. The population consists of 90 participants with work-related chronic stress complaints. The research groups are: (i) intervention group; (ii) placebo group; and (iii) control group. Participants in the intervention group will be treated with light therapy/pulsed electromagnetic field therapy for 12 weeks, twice a week for 40 min, and coaching (once a fortnight for 50 min). The placebo group receives the same treatment but with the light and pulsed electromagnetic field switched to placebo settings. The control group receives only coaching for 12 weeks, a course of six sessions, once a fortnight for 50 min. The primary outcome is the level of return to work. Secondary outcomes are fatigue, stress and quality of life. Outcomes will be measured at baseline, 6 weeks, 12 and 24 weeks after start of treatment.

**Discussion:**

This study will provide information about the effectiveness of coaching and light therapy plus pulsed electromagnetic field therapy on return to work, and secondly on fatigue, stress and quality of life in people with work-related chronic stress.

**Trial registration:**

NTR4794, registration date 18-sept-2014

## Background

Work-related chronic stress (burnout) is the psychological concept of having high work demands and the feeling of being exhausted, having no energy or motivation for performing activities related to work, and will lead in most cases to partial failure or even to complete breakdown [1]. The term burnout was used for the first time in the early 1970s by the American psychotherapists Herbert Freudenberger and Christina Maslach [2], with their theory becoming dominant in the field. According to Maslach, burnout consists of three more or less related phenomena: (i) exhaustion (a feeling of extreme tiredness); (ii) cynicism (distance to work, or to the people with whom one works); and (iii) reduced personal accomplishment (the feeling of being less able to carry out work, including reduced work-related self-confidence). People who have a burnout have little energy to start new activities, feel exhausted and are no longer able to carry out work. The incidence of severe strain in work-related chronic stress was estimated at 307 per 100,000 workers in the Netherlands in 2011 [3]. Work-related chronic stress is an increasing problem for workers and employers and the costs to society are substantial [4].

The regular approach for workers with work-related chronic stress complaints with sickness absence is mental coaching, based on cognitive-behavioural insights [5]. In the coaching sessions, factors are identified that influence the occurrence of the symptoms. These factors are then addressed to alleviate the symptoms. A treatment consists of several stages. In the initial phase of therapy, reduction of symptoms and global recovery are the primary targets. The condition improves and physical symptoms are reduced. The subsequent phases consist of teaching skills and researching dysfunctional thoughts that perpetuate the symptoms. These last two phases can be reversed in sequence.

Light therapy appears to be effective in reducing fatigue in burnout [6], while the treatment with a weak magnetic field (Pulsed Electro Magnetic Field, PEMF) has been used with some success in treatment-resistant depression [7] and pain [8]. The combination of light therapy and electromagnetic field therapy in the treatment platform Xentix [9] is a promising additional treatment. Light therapy is known to stabilize the sleep/wake rhythm and this may result in increased energy and reduced fatigue. Pulsed Electromagnetic Field therapy stimulates the metabolism, creating a better balance between the cell and the intercellular space [10]. Hormones and neurotransmitters move from one cell type to another and carry chemical “messages” that modulate the metabolic responses of tissues to the environment. Interaction with these signalling systems is a potential mechanism by which very low-energy electromagnetic fields might produce metabolic responses in the body. Hormone and neurotransmitter receptors are specialized protein molecules that use a variety of biochemical activities to pass chemical signals from the outside of a cell across the plasma membrane to the interior of the cell. Since many low-energy electromagnetic fields have too little energy to directly traverse the membrane, it is possible that they may modify the existing signal transduction processes in cell membranes, thus producing both transduction and biochemical amplification of the effects of the field itself [11]. The current state of knowledge of the physiological mechanisms of PEMF remains limited however.

Both light therapy for burnout [6] and magnetic field therapy in fibromyalgia [12] show a positive effect on emotional exhaustion, one of the main symptoms of burnout. Light therapy also has a positive effect on fatigue and quality of life in patients with SAD (Seasonal Affective Disorder SAD) and winter blues (Sub-Syndromal Seasonal Affective Disorder S-SAD) [13, 14]. In Multiple Sclerosis (MS), a positive effect of light therapy has been seen on fatigue [15, 16] and of magnetic field therapy on quality of life [17]. It is expected that the intervention with coaching and light therapy plus magnetic field therapy will lead to a faster return to work and increased reduction of stress levels and fatigue. This could lead to an improvement in the degree of work participation and of the quality of life. Consequently, medical consumption is thought to be reduced.

The aim of this study is to establish whether an approach incorporating coaching supplemented by light therapy plus pulsed electromagnetic field therapy in people with work-related chronic stress symptoms contributes to earlier return to work compared to guidance with coaching only. A secondary aim is to assess the effect on the reduction of fatigue, chronic stress and quality of life.

## Methods

### Study design

The study is a three-armed randomized placebo-controlled trial (RCT) with patients with work-related chronic stress (*n* = 90). Subjects with the aforementioned problems are treated in three groups: (i) group 1 receives light therapy/electromagnetic field therapy and coaching (CoLMF group); (ii) group 2 receives the same treatment conditions but the light therapy/electromagnetic field therapy is not activated (CoPL group); and (iii) group 3 will receive coaching only (Co group).

### Setting

The study will be performed in a treatment centre in Eindhoven, the Netherlands that has been built and equipped specifically for this study. An advanced light therapy/magnetic therapy treatment platform was developed in Belgium, which, in combination with coaching, might alleviate the symptoms in people suffering from work-related chronic stress. The centre offers five treatment rooms where the treatment equipment is set up, and two rooms for coaching. The staff consists of researchers, coaches and trained assistants. The device used in the study is a reclining chair with a lengthened seat forming a leg rest (see Fig. 1). It forms a comfortable treatment platform with a light therapy unit mounted above the participant’s head. The electromagnetic coils are situated in the pillow and bed. During the treatment, the participants lie on the bed. Their eyes are closed so that the light reaches the retina through the eyelids. In the case of high photosensitivity of the participant, dark goggles can be worn.

**Fig. 1 Fig1:**
[figure not shown]
Xentix treatment platform

### Study population

The population consists of employees (18–65 years of age) from the south of the Netherlands (Eindhoven region) with work-related chronic stress complaints with at least 50 % absenteeism.

### Recruitment of the participants

Participants are recruited through social media, newspapers, general practitioners and through an occupational health service. Prior to the recruitment of participants, all staff will be informed.

### Inclusion criteria

Employees with work-related chronic symptoms aged between 18 and 65 years with at least 50 % sickness absenteeismDiagnostic criteria for neurasthenia (symptoms 0–6 months)Speaking the Dutch language

### Exclusion criteria

PregnancySerious somatic problems such as diabetes or epilepsySerious ocular diseasesConfusion or severe gloomUse of psychotropic drugs other than selective serotonin reuptake inhibitors SSRIsPacemaker/neuro-stimulators

### Informed consent and randomization

Randomization (Fig. 2) will take place once the participant meets the inclusion criteria, has read the written information about the study and has given written informed consent after approval and after the baseline measurements. Preliminary numbers are assigned to the three groups of equal size in the study. Participants receive a random number from a research assistant who is not involved in the actual measurements. These numbers are printed on the measuring instruments. Participants are given a random number on the basis of entry and assigned to one of the three groups.

**Fig. 2 Fig2:**
[figure not shown]
Study design

### Blinding

The RCT is single-blinded in the sense that none of the outcome assessors are aware of the group assignment of the subjects. Furthermore, because of the use of a placebo-controlled group, in two out of the three groups the participants are double-blinded.

### Intervention

#### Coaching

The regular guidance during mental coaching sessions of people with work-related chronic stress is a cognitive-behavioural approach [18, 19]. A standard guidance protocol is used by certified coaches (BSc, MSc) who were originally trained as work and organization psychologists, clinical therapists or mental health counsellors. In addition, they have all been additionally trained as a mental coach. The guidance helps in identifying and solving the problems the employee has. During coaching, the three stages of recovery are defined: (i) acceptation and relaxation; (ii) increasing employability; and (iii) support to return to work. The guidance consists of a number of regular and elective modules. The key components of the modules are: (i) to reduce symptoms; (ii) solution focused therapy; and (iii) relapse prevention. Additionally, time management, organisation-focused interventions, conflict management, psycho-education and ways to influence fatigue and restore the balance between capacity and payload are mainly addressed. Participants are taught to set new personal goals and to achieve them.

#### Light therapy

Electromagnetic energy consists of a combination of coherent and incoherent light. The coherent light is generated through multiple high-performance LEDs (light emitting diodes) with wavelengths of 470 nm (blue), 525 nm (green) and 570 nm LED (yellow). The non-coherent light is generated by means of an optically-centred halogen lamp with a light output of +/− 9000 lumens. The maximum illuminance at the eye is +/− 6000 l×. The light is directed by means of facetted and coated reflectors and then linearly polarized. Ultra Violet (UV) and Infra-Red (IR) wavelengths are filtered out of the spectrum. An important role is played by a specific type of ganglion cell in the retina involving intrinsic light-sensitive retinal ganglion cells Ip-RGC (intrinsic photo-sensitive retinal ganglion cells). Like other retinal ganglion cells, these are concerned with processing information collected by the rods and cones. One of the differences with the other ganglion cells is that Ip-RGCs also are directly sensitive to light. They contain the photosynthetic pigment melanopsin, which is most sensitive to blue-green light (absorption maximum near 480 nm). Another difference relates to anatomy. Ip-RGCs appear at various locations in the retina, and they project to several specific areas in the brain. One target of the projections of the Ip-RGCs is the Suprachiasmatic Nucleus (SCN), also known as the biological clock.

#### Pulsed electro Magnetic field therapy PEMF

The weak magnetic fields are generated in the apparatus using low voltage in multiple coils that are integrated and spread over the sofa and in the pillow set. The magnetic fields are wide-band and the amplitude of the magnetic fields is almost constant across the whole of the frequency band used. The specific frequency band is in the ELF (extremely low frequency, 0-30Hz) and the ULF (ultra-low frequency, 30–30,000Hz) ranges. The maximum magnetic flux density B = 0.3 Wb/m^2^ = 0.3 T. The principle of operation is hypothesized to be due to a better cell metabolism whereby ions are transferred more quickly and easily between the cell and the intercellular space.

#### Frequency and duration of the interventions

Participants will be treated for 12 weeks, twice a week for 40 min on the treatment platform with light therapy/magnetic field therapy, with coaching being given 50 min every fortnight during a 12-week period (CoLMF group 1). The placebo group receives the same treatment condition but the light and magnetic field are switched off (CoPL group 2). The control group receives coaching only (Co group 3), also 50 min once a fortnight during a 12-week period.

#### Control interventions

The participants allocated to the placebo group (2) will undergo treatment at the treatment platform but with the magnetic field switched off. Only a non-effective, small dose of coherent/incoherent light > 5 lx is used to give the impression that the apparatus is working. The participants allocated to the coaching group (3) receive regular guidance in coaching sessions given by a certified coach.

### Outcomes

#### Primary outcome

The primary outcome variable is the percentage return to work: the number of contract hours that participants work at the end of the study compared to the number of contract hours worked in the week prior to the study (T0). The number of hours worked will be measured at T0 (start), T2 (after 12 weeks) and T3 (after 24 weeks).

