#### Sample size

The sample size is based on a medium effect size on the primary outcome of the intervention, return to work. Changes in the outcome measures are measured across the three groups and four measuring points by comparing them at the start of the study (T0) with the outcome measures after the end of the measurement period (T3). In order to determine the differences within and between the four measurement points, a multilevel regression analysis is conducted. For a power of 0.80 with an effect size of f = 0.3, the number of participants required is *N* = 79, with *N* = 90 being a desirable starting figure.

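### The percentage return to work names only the hours worked just before T0 as its reference, and the entry criteria allow those hours to be zero

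*Protocol article*

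**What the plan says.** The Primary outcome section of the protocol article reads: "The primary outcome variable is the percentage return to work: the number of contract hours that participants work at the end of the study", and continues "compared to the number of contract hours worked in the week prior to the study (T0". It adds the measurement times: "The number of hours worked will be measured at T0 (start), T2 (after 12 weeks) and T3 (after 24 weeks". No other reference quantity is named there.

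The Study population section admits employees "with work-related chronic stress complaints with at least 50 % absenteeism". The Inclusion criteria repeat this threshold. Neither sets an upper limit, and the Exclusion criteria do not mention full absence.

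The Sample size section rests on the primary outcome: "For a power of 0.80 with an effect size of f = 0.3", "the number of participants required is *N* = 79", with 90 to be started. It plans a multilevel regression that compares T0 with T3: "Changes in the outcome measures are measured across the three groups and four measuring points".

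The Informed consent and randomization section places randomization after the baseline measurements.

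The article nowhere makes total contract hours the base of the percentage, and it gives no rule for a participant who worked no hours before T0.

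**The concern.** A percentage needs a base. The only candidate in the definition is the number of hours actually worked when the participant was already sick-listed. For a fully absent worker that base is zero. For a mostly absent worker it is small, so the percentage measures growth from a low start and not the degree of return. The abstract, by contrast, describes the primary outcome as a level of return to work.

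This is the endpoint on which the sample size rests. If the definition is applied as written, some eligible participants have no primary value. If it is not, the analyst must choose between readings that order participants differently, and the article does not fix that choice before data are seen.

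**Working it through.** **The plan's own figure.** The stated inputs are f = 0.3, power 0.80 and three groups; neither alpha nor the correlation between repeated measures is given. A one-way comparison of three groups at an assumed alpha of 0.05 needs N = 111. A repeated-measures comparison between groups has noncentrality λ = f²·N·m / (1 + (m − 1)ρ). With m = 4 points and ρ = 0.6, the smallest N reaching 0.80 is 79: λ = 0.09 × 79 × 4 / (1 + 3 × 0.6) = 28.44 / 2.8 = 10.16. With m = 2 and ρ = 0.4 it is also 79: λ = 14.22 / 1.4 = 10.16. So 79 is attainable but is not fixed by the stated inputs. Below it serves only as the number the plan says it needs.

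**Range of T0 hours.** Let c be contractual weekly hours, w0 the hours worked in the week before T0, and w3 those at T3. Absence between 50 % and 100 % gives 0 ≤ w0 ≤ 0.5c.

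**Literal ratio.** R = 100 × w3 / w0.

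- If w0 = 0, R is undefined whatever w3 is.
- If w0 > 0, the T0 value is 100 × w0 / w0 = 100 % for everyone. It has no variance and cannot act as a measurement point in the planned longitudinal model.
- A full return (w3 = c) scores 100 × c / w0, which is at least 200 %.
- With p0 = w0/c and p3 = w3/c, R = 100 × p3 / p0. Contract size cancels, so the pattern below does not depend on the 40-hour contract assumed for illustration.

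| Hours T0 → T3 (c = 40, assumed) | Ratio to T0 hours | Difference | Share of contract at T3 |
|---|---|---|---|
| 0 → 40 | undefined | 40 h | 100 % |
| 0 → 20 | undefined | 20 h | 50 % |
| 0 → 0 | undefined | 0 h | 0 % |
| 20 → 40 | 200 % | 20 h | 100 % |
| 4 → 8 | 200 % | 4 h | 20 % |
| 4 → 20 | 500 % | 16 h | 50 % |
| 20 → 20 | 100 % | 0 h | 50 % |

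On the ratio, a full return from half absence ties with 4 → 8 h and falls below 4 → 20 h.

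**Difference in hours.** D = w3 − w0 exists for everyone, but it is not a percentage. A full return from complete absence gives D = c, so it scores 40 on a 40-hour contract and 20 on a 20-hour contract.

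**How many could be affected.** The share fully absent at T0 is not in the article. The margin is 90 − 79 = 11 participants, or 11/90 = 12.2 %. Twelve zero baselines (12/90 = 13.3 %) leave 78. For assumed shares:

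| Assumed share with zero T0 hours | Undefined of 90 | With a value |
|---|---|---|
| 10 % | 9 | 81 |
| 30 % | 27 | 63 |
| 50 % | 45 | 45 |
| 70 % | 63 | 27 |

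These counts allow for no other loss. Any dropout would draw on the same margin of 11.

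**The case against.** The text speaks of comparing, not of dividing. Hours are to be measured at T0 in their own right, and the Sample size section compares T0 with T3 in a multilevel model. A ratio to T0 fits that model badly; hours, or the share of contract hours, at each time point fits it well. The definition also counts contract hours, and the 50 % absence criterion itself needs a working-hours base. The authors may therefore have meant a share of contract, and a fuller protocol may say so.

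Much of this stands. A reader might infer that the plan definitely divides by T0 hours and that the endpoint therefore cannot be computed. The article does not support that certainty. What remains is that the outcome is called a percentage, only T0 hours worked are named as its reference, and a contract-hours base is nowhere stated. That is a stated definition that fails for eligible participants, not detail left to another document: an analysis plan using contract hours would have to replace the sentence.

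Three further inferences are tempting and go too far:

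- That the ratio always misranks participants. It does so for some pairs, not for every pair.
- That a few near-zero baselines will drive the result. The article gives no distribution of T0 hours; the 4-hour baseline is chosen for illustration.
- That dropping undefined cases biases the comparison of arms. T0 hours are fixed before randomization, so excluding on them removes the most absent workers and costs power and generalisability, but does not by itself unbalance the arms.

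**Conclusion.** The concern holds as a defect in the stated definition. Under the literal ratio, the primary outcome is undefined for every participant with zero T0 hours, is constant at T0 for the rest, and can place a 20 % or 50 % return level with or above a full one. Under the difference reading it is computable, but it is not the percentage announced and it varies with contract size. The article does not settle which is meant.

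The undefined values and the tied rankings follow from the definition and the entry criteria for any contract size. How many participants are affected is not known. The only firm threshold is that 12 or more zero baselines among 90 would take the number with a primary value below 79; the other counts rest on assumed shares. The consequence is an unfixed primary endpoint with possible loss of power and generalisability. Bias between arms is not shown.

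**What to change.** Replace the definition with: 100 × hours worked in the reference week / contractual weekly hours fixed at T0, counting no more than the contractual hours, so that the value lies between 0 and 100 %. Compute it in the same way at T0, T2 and T3. Name T3 as the primary time point, and use the T0 value as the baseline in the longitudinal model.

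Every row of the first table above then has a value, and the values are ordered by the degree of work resumed. T0 becomes a usable measurement, running from 0 to 50 % under the entry criteria.

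The cost is one baseline item, contractual weekly hours, which the 50 % absence criterion already requires someone to know. Because the trial is registered and has ethics approval, the change should be recorded as a dated clarification of the registered outcome, made before outcomes are compared by arm. One point to watch is that a bounded outcome may pile up at 0 and 100 %, so the model's residual assumptions need checking. Treatment and visits do not change.
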